### Study design

The effects of the implementation of a PHR in maternity care on patients and professionals will be identified in a stepped-wedge, cluster-randomised, controlled trial. This type of trial is suitable for studying the effects of a new intervention, which is implemented at the cluster level, but experienced and measured by its impact on individuals [11, 12]. In essence, a stepped-wedge trial randomly allocates clusters to groups that crossover from a control condition to an intervention at different crossover points. In the present study, all healthcare professionals, working at 13 sites (11 community-based midwife practices and two hospitals, comparable in the number of patients) agreed to participate. Following baseline measurements, sites will be randomly assigned to four groups, containing three or four sites. The two hospitals are randomly allocated to group 1 and group 2; groups 3 and 4 contained only community-based midwife practices. The length of time between the two successive crossover points is 3 months. The total trial duration is 21 months. Figure 1 illustrates the study over time, including a pre-rollout period, four crossover points, and a post-rollout period. At the start of the study, all sites belong to the control group; at the end of the study, all sites belong to the intervention group. Data collection will be performed in all steps along the trial, coinciding with all four crossover moments.

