### Outcome measures

The primary outcome measure in this study is health outcomes in maternity care. We will use a composite maternal/neonatal outcome measure: the total proportion of uncomplicated pregnancies/births. This includes the following conditions: gestational age at time of delivery is 37–41 weeks, spontaneous start of contractions, spontaneous rupture of membranes, no help during delivery, weight of neonate 5–95 %, APGAR score after 5 min > 7, and no serious postpartum haemorrhage.

Secondary outcome measures are the quality of care from the patients’ perspectives, collaboration among healthcare professionals, and the adoption of MyPregn@ncy by patients and professionals.

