### Measurements

Table 1 presents an overview of all measurements used.

**Table 1 Tab1:** Overview of outcome measures with accompanying methods and measurements

Outcome measure	Study population	Method	Instrument	Time of measurement
Healthcare	All pregnant women in care in the area	Database	Perinatal Data Register	Five times, along all successive steps of the study
Quality of care	All pregnant women in care in the area	Survey	Questionnaire ReproQ	Five times, along all successive steps of the study
Collaboration	All maternity care healthcare professionals in the area	Survey	Social Network Analysis	Baseline and one post measurement
Adoption	All users of MyPregn@ncy	Log format, Survey, Interview	Log data, Questionnaire, Topic list	During and after implementation

The total proportion of uncomplicated pregnancies/births will be based on data from the Dutch Perinatal Registry (PRN). In the Netherlands, more than 95 % of all births and accompanying perinatal outcomes are centrally registered in this large national database [10].

The quality of care from the patients’ perspectives will be measured by an adapted version of the questionnaire ReproQ [15]. This new questionnaire has been developed to evaluate the whole maternity care, regardless of where the care is given [15, 16]. Development of this self-report questionnaire has been based on the 8-domain WHO Responsiveness model, including the following domains: dignity, autonomy, confidentiality, communication, prompt attention, social consideration, basic amenities, and choice and continuity [17]. The original questionnaire consists of two parts with largely identical questions: an antepartum questionnaire and a postpartum questionnaire. Due to considerations of time and response, we will use a combined version of both questionnaires in the present study, 6 to 10 weeks postpartum. Subgroups of participants in the study groups will be invited to complete the ReproQ in every phase of the stepped-wedge design. The results of the questionnaires will be calculated in domain scores and overall scores, ranging from one to four [15]. PRN data and ReproQ data will be collected during each step of the stepped-wedge study.

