### Statistics

Sample size calculations have been based on an expected improvement of 47 % to 60 % in the proportion of uncomplicated births. Combined with an alpha of 0.05, 80 % power, and a design effect (correction factor due to a stepped-wedge design [21]) of 0.62, a total of 305 pregnant women is necessary for each step. With 13 sites and an expected uptake rate of 25 %, 84 pregnant women/step/site are needed to measure the effects.

Data analysis for the stepped-wedge design will be performed according to an intention-to-treat protocol at the end of the study period, once all sites have at least completed one 3-month intervention period. Individual PRN and ReproQ data will be combined with the different sites. To estimate the intervention effect on the outcome measures, a standard mixed-model approach will be used. The mixed model will incorporate fixed terms for intervention (before versus after), time (3-month period), as well as a correlation of repeated measurements over time as random effects. Hence, the analyses will have the element of a time-series analysis with multiple time points before and after the intervention. Analyses will be performed using SPSS (version 20.0 for Windows: SPSS Inc., Chicago, IL, USA).

Description of the network data by Social Network Analysis (SNA) involves visual analysis of network diagrams produced using a specific software program, NetDraw [22]. This software converts matrices of network data into diagrams and individual nodes using complex algorithms. We will use UNICET v6 [19] to construct the network and obtain network parameters and SPSS 20 (SPSS Inc., Chicago, IL, USA) for statistical analysis.

In addition to log data analysis, the interviews will be audiotaped and transcribed verbatim. The interviews will be independently coded by two persons based on the topic list.

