## Discussion

The presented paper describes the design of a study in which a PHR will be offered to pregnant women and their healthcare professionals in order to improve health outcomes, to improve patients’ experiences with maternal care, and to achieve more collaboration between healthcare professionals. As far as we know, this study is the first to implement a PHR in maternity care. The study is expected to yield new information about the strengths, possibilities, and challenges to the implementation and usage of a PHR in maternal care settings. Results may lead to new insights and improvements in the quality of maternal and perinatal care.

The present study has several strong aspects. Earlier experiences with PHRs on the platform www.mijnzorgnet.nl have shown promise for more extensive use [13]. In addition, patient representatives have been consulted in the development of the implementation strategy. Furthermore, the choice of a stepped-wedge study design rather than a standard, randomised, controlled trial takes into account the actual different levels of implementation (cluster level) and experience and measurements (individual level).

We realise the study has some aspects that could have been more optimal. Ideally, the patient representatives should have included pregnant women. Furthermore, a pilot study preliminary to the present study would have contributed to a more detailed preparation. Finally, the study design has several limitations. We realise that a 3-month period for each step might be short for the measurement of an effect. However, we made this choice deliberately, balancing among the number of steps, length of each interval, and total length of the study. Our overall focus in this choice was to perform a well-designed study in a practical time setting. Additionally, the study region has only two hospitals. Due to the multidisciplinary aspect of the intervention, hospitals should be present early in the intervention group. Therefore, we have chosen to randomly allocate the two hospitals to group 1 and group 2, whereas groups 3 and 4 contained only community-based midwife practices. By doing this, we are well aware of the potential underlying differences in treatment effect among the patient populations. Therefore, we will focus special attention for this confounding effect in the analyses.

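### The stated primary model names no prognostic covariate and no hospital/practice term, although the Discussion promises attention to that confounding; the model is valid but loses some precision and can carry a small shift

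*Protocol article*

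**What the plan says.** All references are to the protocol article.

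- **Statistics, fixed part:** "The mixed model will incorporate fixed terms for intervention (before versus after), time (3-month period" are the terms given. No covariate of the woman or the site is named there or elsewhere in the article.
- **Statistics, random part:** the model is completed by "as well as a correlation of repeated measurements over time as random effects". The unit that carries this correlation is not named. The same paragraph says that individual register data will be linked to the sites.
- **Outcome measures:** the primary outcome is "the total proportion of uncomplicated pregnancies/births", which each pregnancy contributes once.
- **Measurements, Table 1:** register data are collected "Five times, along all successive steps of the study".
- **Study design:** there are "13 sites (11 community-based midwife practices and two hospitals, comparable in the number of patients". These "sites will be randomly assigned to four groups, containing three or four sites", with one restriction: "The two hospitals are randomly allocated to group 1 and group 2; groups 3 and 4 contained only community-based midwife practices".
- **Discussion:** the restriction is explained, possible differences among the patient populations are acknowledged, and the article states: "Therefore, we will focus special attention for this confounding effect in the analyses". It names no variable and no method.

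**The concern.** Two separate matters follow from these statements.

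**Precision.** The women at one step are not the women at the next, so the random term cannot be a within-woman correlation. Even read as a site effect, it absorbs only differences between sites that stay constant, and the period terms absorb only changes shared by all sites. Variation in who gives birth at a given site in a given step stays in the residual. Characteristics fixed before exposure could explain part of it.

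**Built-in imbalance.** Hospitals sit only in groups 1 and 2, so over five periods they contribute 4 and 3 intervention periods. Sites in groups 3 and 4 contribute 2 and 1. The Setting section says that women with risk factors or complications are referred to secondary or tertiary care, so the two kinds of site may well have different rates of uncomplicated birth. The Discussion recognises this, but nothing in the model as stated acts on it. If the choice is made after the data are seen, the promised attention becomes a post hoc decision.

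**Working it through.** **1. The plan's own figure.** Inputs from Statistics: 47 % versus 60 %, alpha 0.05 (taken as two-sided), power 80 %, design effect 0.62. The two-proportion formula gives 230 per arm, or 246 with continuity correction.

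- With correction: 2 × 246 × 0.62 = 305.04, which reproduces the stated 305 per step.
- Without correction: 2 × 230 × 0.62 = 285.2, which does not.

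This point does not contest the 305. Spread over 13 sites it is 305/13 = 23.5 women per site and step. The article also gives 84 per site and step before uptake, so both sizes are used below.

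**2. Precision lost without covariates.** The article gives no prognostic strength, so a range is assumed for one covariate, first versus later birth: share q = 0.45, and a difference d of 10 to 30 points in the uncomplicated rate. With p = 0.47,

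R² = q(1−q)d² / [p(1−p)] = 0.2475 d² / 0.2491.

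| d | R² | SE reduction, 1 − √(1−R²) |
|---|---|---|
| 0.10 | 1.0 % | 0.5 % |
| 0.20 | 4.0 % | 2.0 % |
| 0.30 | 8.9 % | 4.6 % |

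A generalised least squares calculation agrees. It used 13 sites in groups of 4, 3, 3 and 3 (which group has four is assumed), five periods, a random site intercept, and binomial variance at 53.5 %. At 23.5 women per site and step and an intracluster correlation (ICC) of 0.05, power for 47 % versus 60 % is 0.85 unadjusted, 0.87 if covariates explain 5 % of within-site variance, and 0.88 if they explain 10 %.

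The same effect can be seen in one cell. At 84 women, the first-birth share has a chance SD of √(0.45 × 0.55/84) = 5.4 points. Multiplied by d, this moves a site-step rate by 0.5-1.6 points. That restates the R² in other units and is not an additional loss.

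**3. Shift from the hospital placement.** The same model was fitted without a site-type term, with hospitals given a constant offset below practices (assumed, 10 to 30 points). The estimated effect moves down by a fixed fraction of the offset.

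| Women per site-step | ICC | Fraction | Shift at 10 / 20 / 30 points | SE without → with site-type term |
|---|---|---|---|---|
| 23.5 | 0.01 | 0.1254 | 1.3 / 2.5 / 3.8 | 0.0403 → 0.0409 |
| 23.5 | 0.05 | 0.0459 | 0.5 / 0.9 / 1.4 | 0.0433 → 0.0435 |
| 23.5 | 0.10 | 0.0245 | 0.2 / 0.5 / 0.7 | 0.0431 → 0.0432 |
| 84 | 0.01 | 0.0609 | 0.6 / 1.2 / 1.8 | 0.0230 → 0.0231 |
| 84 | 0.05 | 0.0152 | 0.2 / 0.3 / 0.5 | 0.0236 → 0.0237 |
| 84 | 0.10 | 0.0075 | 0.1 / 0.1 / 0.2 | 0.0232 → 0.0232 |

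With the term in the model the shift is zero. The 3.8-point corner is a ceiling that is hard to reach. With equal site sizes, a 30-point offset in 2 of 13 sites alone gives a between-site variance of 0.09 × (2/13) × (11/13) = 0.0117. That is 0.0117/0.2488 = 0.047 of the total, so an ICC near 0.05 rather than 0.01 would be expected.

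**The case against.** The strongest reply is that a list of baseline covariates is commonly left by an article to the full protocol or analysis plan, so its absence here is no defect. A model with intervention, period and a random part is a recognised stepped-wedge analysis, and nothing in it is wrong. This stands as far as validity goes. What remains is that the article sets out the model's fixed terms and elsewhere promises an adjustment that those terms do not contain.

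A reader might infer three stronger things, and the documents support none of them.

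- **That the model has only two fixed terms.** The text says what the model will incorporate. It does not say that nothing else enters, and the Discussion shows that the authors intended more.
- **That chance differences in case-mix across 13 sites bias the result.** Under randomisation they are imprecision, which the standard error already reflects. The systematic imbalance is the one the allocation builds in, hospital versus practice.
- **That the conclusion could turn on covariates.** A standard error smaller by at most 4.6 % would rarely change a conclusion when the target difference is 13 points.

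A further objection also stands: adjusting for parity and age alone would leave the site-type imbalance untouched, so the remedy must include site type. Finally, the article lists no register fields, so whether any particular covariate is available cannot be confirmed.

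**Conclusion.** The point holds as a low-severity improvement. The stated model is valid, but it names no prognostic covariate and no site-type term, and the Discussion's promise about confounding has no counterpart in the Statistics section.

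- **Precision:** a standard error about 0.5-4.6 % smaller if covariates explain 1-9 % of outcome variance. The first-birth share and the 10-30 point gap behind this range are assumptions.
- **Shift:** about 0.1-3.8 points, most plausibly in the lower part of that range. It rests on an assumed hospital offset of 10-30 points and an ICC of 0.01-0.10. If hospitals have the lower rate, it pulls the estimate against the intervention.

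The shift figures also assume that the random part is a site intercept, which the article does not clearly say. They do not cover a model without a site effect.

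**What to change.** In Statistics, pre-specify these fixed terms:

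- intervention and 3-month period;
- site type (hospital or practice), or site itself in its place, since site already contains site type;
- characteristics fixed before exposure that the individual register record holds, for example first versus later birth, maternal age, and singleton versus multiple pregnancy. Confirm first that these fields exist.

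Define site type by the site that determines whether a woman counts as control or intervention. Do not adjust for referral or place of birth, because the record may change them. Standardise the fitted result to an absolute difference in the proportion of uncomplicated births, so that it can be read against 47 % and 60 %. Keep the model without covariates as a sensitivity analysis. Let the Discussion sentence on confounding refer to this specification.

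The cost is a change of wording and slightly more analysis work, including a stated rule for the few records with a missing covariate, such as a missing category. If the fields are in the register record, no new data are needed. The site-type term costs almost no precision (0.0433 to 0.0435 at 23.5 women per site-step and ICC 0.05).

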## Discussion

The presented paper describes the design of a study in which a PHR will be offered to pregnant women and their healthcare professionals in order to improve health outcomes, to improve patients’ experiences with maternal care, and to achieve more collaboration between healthcare professionals. As far as we know, this study is the first to implement a PHR in maternity care. The study is expected to yield new information about the strengths, possibilities, and challenges to the implementation and usage of a PHR in maternal care settings. Results may lead to new insights and improvements in the quality of maternal and perinatal care.

The present study has several strong aspects. Earlier experiences with PHRs on the platform www.mijnzorgnet.nl have shown promise for more extensive use [13]. In addition, patient representatives have been consulted in the development of the implementation strategy. Furthermore, the choice of a stepped-wedge study design rather than a standard, randomised, controlled trial takes into account the actual different levels of implementation (cluster level) and experience and measurements (individual level).

We realise the study has some aspects that could have been more optimal. Ideally, the patient representatives should have included pregnant women. Furthermore, a pilot study preliminary to the present study would have contributed to a more detailed preparation. Finally, the study design has several limitations. We realise that a 3-month period for each step might be short for the measurement of an effect. However, we made this choice deliberately, balancing among the number of steps, length of each interval, and total length of the study. Our overall focus in this choice was to perform a well-designed study in a practical time setting. Additionally, the study region has only two hospitals. Due to the multidisciplinary aspect of the intervention, hospitals should be present early in the intervention group. Therefore, we have chosen to randomly allocate the two hospitals to group 1 and group 2, whereas groups 3 and 4 contained only community-based midwife practices. By doing this, we are well aware of the potential underlying differences in treatment effect among the patient populations. Therefore, we will focus special attention for this confounding effect in the analyses.

This study is important because of the recently expressed strong wish for an easy and accessible PHR for each citizen in 2020 by the leading healthcare players in the Netherlands. The results of the study can help facilitate this wish and perfectly connects to the current developments in Dutch healthcare.

### Trial status

Community-based midwife practices and hospitals have been included. The study is currently recruiting participants, i.e. individual clients and professionals. The estimated study completion date is April 2016.

## Abbreviations

PHR: personal health record
